## Chapter 14: Adverse Events

---

Azithromycin is being given to these communities under the auspices of the National Trachoma Control programs in each country. They have determined, for programmatic reasons, that widespread coverage with azithromycin is an acceptable community risk for the benefit of eliminating blinding trachoma. Approximately 100 million doses of oral azithromycin have now been distributed for trachoma, and reports of serious side effects are essentially non-existent. This may be due in part to minimal surveillance. In fact, where carefully monitored, there were actually fewer GI side effects after taking azithromycin compared to topical tetracycline, perhaps because azithromycin treats some cases of diarrhea. Azithromycin is generally well-tolerated. The most common side effects of azithromycin and erythromycin are diarrhea or loose stools, nausea, abdominal pain, and vomiting, each of which may occur in fewer than one in twenty persons who receive azithromycin. Rarer side effects include abnormal liver function tests, allergic reactions, and nervousness.

All community residents will be advised to alert the village health worker if they experience, within two weeks of mass treatment, a serious adverse event, defined as diarrhea, nausea and vomiting for more than two days, hospitalization for any cause, or death in a family member. All adverse events will be recorded on a copy of the census list left with the village health worker by the mass treatment teams. These events will be reviewed at the next six month survey, and entered into the adverse event data base for reporting to the Data and Safety Monitoring Committee. If, for any reason, the village resident needs further care, they will be referred to the nearest health center for examination and treatment, and the most appropriate action will be taken to provide immediate care, in accordance with the policies in each country.

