**Table 1: Treatment coverage and frequency randomization arms by country**

| Country    | Frequency of mass treatments                              | No. of communities treated | Coverage                         |
|------------|-----------------------------------------------------------|----------------------------|----------------------------------|
| Niger      | 3 Annual mass treatments                                  | 12                         | 80 – 89% tx coverage $\Upsilon$  |
| Niger      | 3 Annual mass treatments                                  | 12                         | $\geq 90\%$ tx coverage $\Omega$ |
| Niger      | 6 Biannual mass treatments to children ages 12 or younger | 12                         | 80 – 89% tx coverage $\Upsilon$  |
| Niger      | 6 Biannual mass treatments to children ages 12 or younger | 12                         | $\geq 90\%$ tx coverage $\Omega$ |
| Tanzania   | 3 Annual mass treatments                                  | 8                          | 80 – 89% tx coverage $\Upsilon$  |
| Tanzania   | 3 Annual mass treatments                                  | 8                          | $\geq 90\%$ tx coverage $\Omega$ |
| Tanzania   | Stopping rule (Max. 3 Annual mass treatments)*            | 8                          | 80 – 89% tx coverage $\Upsilon$  |
| Tanzania   | Stopping rule (Max. 3 Annual mass treatments)*            | 8                          | $\geq 90\%$ tx coverage $\Omega$ |
| The Gambia | 3 Annual mass treatments                                  | 12                         | 80 – 89% tx coverage $\Upsilon$  |
| The Gambia | 3 Annual mass treatments                                  | 12                         | $\geq 90\%$ tx coverage $\Omega$ |
| The Gambia | Stopping rule (Max. 3 Annual mass treatments)*            | 12                         | 80 – 89% tx coverage $\Upsilon$  |
| The Gambia | Stopping rule (Max. 3 Annual mass treatments)*            | 12                         | $\geq 90\%$ tx coverage $\Omega$ |

$\Upsilon$  Target of 80-90% azithromycin treatment coverage in each community

$\Omega$  Target of greater than 90% azithromycin treatment coverage in each community

\*The stopping rule states that mass treatment will be stopped if trachoma infection is less than 5% of the sample. There is a maximum of three annual mass treatments.

•100 children per community are randomly selected to represent the village prevalence of infection, disease

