## 18.3 DSMC Key Responsibilities

The DSMC will be responsible for carrying out the following responsibilities:

- Reviewing and approving the trial protocol and plans for data and safety monitoring
- Assessing data quality, including completeness
- Monitoring recruitment and losses to follow-up
- Monitoring compliance with the treatment protocol by villages and investigators
- Monitoring evidence for intervention differences in the main outcomes
- Monitoring the safety of interventions (e.g., adverse events)
- Deciding whether to recommend that the trial continues as planned or whether treatment should be terminated in some treatment groups
- Reviewing proposed major modifications to the study prior to their implementation (e.g., increasing target sample size, dropping an arm based on other trial outcomes or toxicity results).
- Suggesting additional data analyses

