## **18.5 DSMC Meetings**

The DSMC will meet once per year, at the start of the project, and once per year thereafter when there is data to review. Additional DSMC teleconferences will be scheduled as the Chair recommends. The agenda will be prepared by the DSMC chair in consultation with the study investigators.

At least five days before the DSMC the Study Principal Investigator will send to the DSMC members a binder of study materials via Federal Express to allow the members' time to review the material before the meeting. The binders will include a set of data reporting tables, shown in Appendix 3. In keeping with confidentiality, the DSMC members will return the binder of materials to the Principal Investigator at the close of the meeting. The Study Principal Investigator and her team will be responsible for the preparation of meeting materials and all DSMC meeting arrangements.

Open sessions of the DSMC meeting may be attended by DSMC voting members, and the non-voting members, and key study team members from each of the clinical sites. Other members of the PRET study team may also be asked by the DSMC chair to attend.

Closed sessions of the DSMC will be attended only by the voting DSMC members, the Executive committee, and the three study statisticians. The closed session may be called when the DSMC reviews the safety and impact data unmasked as to random assignment. At the discretion of the DSMC chair, the committee can meet in Executive session with only the four voting members present to discuss issues and take formal votes as needed.

Minutes will be prepared by the Study Principal Investigator for the antibiotic trial, and the study project director for the surgery trial. Draft minutes will be combined and distributed to the DSMC chair for review and changes before distribution to the entire committee. The minutes shall summarize all recommendations.

Members must make every effort to attend DSMC meetings. If a member fails to make a meeting, it should be ensured that the member makes the next meeting. If a member fails to make the second meeting, the member will be replaced.

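### Serious adverse events are collected only in the two weeks after a treatment round, so observation time differs by frequency arm: counts are not comparable between arms, and rates per window repair this only in part

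*Protocol*

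**What the plan says.** Protocol, Chapter 14, asks residents to report an event only in a fixed period after treatment: "All community residents will be advised to alert the village health worker if they experience, within two weeks of mass treatment, a serious adverse event". The definition that follows is all-cause: "within two weeks of mass treatment, a serious adverse event, defined as diarrhea, nausea and vomiting for more than two days, hospitalization for any cause". Death in a family member also counts. No causality assessment is described. Reporting is open to everyone, treated or not: "All community residents will be advised to alert the village health worker if they experience". The recording tool comes with the treatment visit: "All adverse events will be recorded on a copy of the census list left with the village health worker by the mass treatment teams". The events are reviewed at the next six-month survey and entered in a database for the DSMC.

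The number of rounds is set by the randomized frequency arm. Table 1 (Section 4.2) gives "6 Biannual mass treatments to children ages 12 or younger" in one Niger arm and "3 Annual mass treatments" in the other. Under the stopping rule in Tanzania and The Gambia the maximum is three. Section 4.4.1 expects 40% to 80% of stopping-rule communities to stop after one or two rounds. Section 8.6 restarts a stopped community if infection returns to 20% at the 12 or 18 month survey.

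The DSMC reviews adverse events at each meeting (Section 18.2). Section 18.5 provides for review by arm: "The closed session may be called when the DSMC reviews the safety and impact data unmasked as to random assignment". Its duties in Section 18.3 include "Deciding whether to recommend that the trial continues as planned or whether treatment should be terminated in some treatment groups".

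**The concern.** The window opens only when a treatment team visits, so the randomized factor fixes how long each community is observed for safety. Any hospitalization and any family death count, so some of what is recorded is background illness, which accumulates with observation time whatever the drug does. An arm with more rounds will record more such events.

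The error can run either way. Background events alone could make the biannual arm look harmful. Equally, a real reduction in illness under biannual treatment could be hidden, because half the event rate over twice the time gives the same count. Chapter 14 itself suggests that azithromycin may treat some diarrhea.

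Later tabulation cannot fully repair this. Nothing is collected as an adverse event in annual grappes around months 6, 18 and 30, or in a stopped community after its last round.

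**Working it through.** **Windows per arm.** Counted from the visit schedules in Section 7.6 and agreeing with Table 1. Observed time = 2 weeks x rounds; three years = 3 x 52 = 156 weeks.

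| Arm or community | Rounds (months from start) | Windows | Weeks observed | Share of 156 weeks |
|---|---|---|---|---|
| Niger biannual | 0, 6, 12, 18, 24, 30 | 6 | 12 | 7.7% |
| Annual, all countries | 0, 12, 24 | 3 | 6 | 3.8% |
| Stopped on the 18-month survey | 0, 12 | 2 | 4 | 2.6% |
| Stopped on the 6-month survey | 0 | 1 | 2 | 1.3% |

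Section 8.6 also has all communities treated after the last three-year survey. That round is not counted here; it would add one window to each arm in Tanzania and The Gambia.

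**Stopping-rule arm as randomized.** Mean windows = p x r + (1 - p) x 3, where p is the share that stops (0.4 to 0.8, Section 4.4.1) and r is the rounds received (1 or 2). Re-treatment is ignored.

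- p = 0.8, r = 1: 0.8 + 0.6 = 1.4 windows; annual to stopping arm 3/1.4 = 2.14
- p = 0.8, r = 2: 1.6 + 0.6 = 2.2; ratio 1.36
- p = 0.4, r = 1: 0.4 + 1.8 = 2.2; ratio 1.36
- p = 0.4, r = 2: 0.8 + 1.8 = 2.6; ratio 1.15

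The arm therefore has 13% to 53% fewer windows than the annual arm.

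**Effect on counts with no drug effect (Niger).** Section 4.3 gives an average of 375 people per grappe, and there are 24 grappes per frequency arm: 24 x 375 = 9,000 residents. Person-years observed are 9,000 x 6/52 = 1,038 (annual) and 9,000 x 12/52 = 2,077 (biannual). The protocol gives no background rate, so a range is assumed.

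| Assumed events per 1,000 person-years | Annual count | Biannual count | Per window, either arm |
|---|---|---|---|
| 5 | 5.2 | 10.4 | 1.73 |
| 10 | 10.4 | 20.8 | 3.46 |
| 20 | 20.8 | 41.5 | 6.92 |
| 50 | 51.9 | 103.8 | 17.31 |

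The count ratio is 2.0 throughout. The ratio per window is 1.0, but only if the background rate is the same in every window.

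**Why a rate per window is only a partial repair.**

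- *Season.* Three of the six biannual windows (months 6, 18, 30) have no concurrent window in annual grappes. If illness varies by season, the rate per window is still confounded.
- *Age.* In biannual grappes only children aged 0-12 are treated (Section 8.2.1), yet all residents report. A rate over all ages mixes treated children with untreated older residents in one arm only.
- *Stopped communities.* There is no window after the last round, so there is nothing to divide.

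**The case against.** A reader might infer that the safety figures shown to the DSMC are biased by design. The protocol does not support that. It never says that arms are compared on crude counts and sets no test or threshold for adverse events. The DSMC tables are in Appendix 3, whose contents are not shown; they may give rates per round. The DSMC includes a biostatistician and would know that one arm had twice the rounds. The Section 18.3 duty on terminating treatment does not name safety data as its basis, and the DSMC is advisory.

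A reader might also calculate a false-alarm probability. For the counts above, an exact two-sided 5% test of equal counts would reject in about 19%, 39%, 72% and 99% of trials; a Wald approximation gives 25%, 45%, 73% and 98%. These figures belong to a test that the protocol does not propose. They also ignore clustering by grappe, assume complete reporting and rest on assumed rates, so nothing here depends on them.

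A two-week window after a single oral dose is a reasonable way to capture acute drug effects. Extra drug-caused events from six rounds are a true consequence of that strategy; only the background part is an artefact. The figure of one or two windows describes a community that stops and is not restarted, not the randomized stopping-rule arm. Deaths are also recorded through the census in every arm, although Chapter 14 does not route those records to the adverse event database.

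All of this stands. It narrows the point without removing it: events that were never collected cannot be recovered by a better table.

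**Conclusion.** The concern holds in a limited form. Chapter 14 makes ascertainment time depend on the randomized frequency arm: 6 windows biannual, 3 annual and about 1.4 to 2.6 on average under the stopping rule before re-treatment. All-cause counts are therefore not comparable between frequency arms (2:1 biannual to annual with no drug effect; 1.15 to 2.14 annual to stopping rule). Rates per window correct the time imbalance but not season, age mix or the absence of data after stopping.

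The window counts and the 40%-80% stopping share come from the protocol. The 2:1 ratio assumes a constant background rate and equal reporting in every window. Within a frequency arm both coverage targets have the same planned rounds, so the coverage comparison is affected only through stopping. The primary outcome, sample size and randomization are untouched. This is a safety-ascertainment weakness that should be corrected.

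**What to change.** 1. **Collection (Chapter 14).** Leave the same two-week event list with the village health worker after every six-monthly survey in every community, whether or not treatment is given, with the same advice to residents. State the start date: the treatment date where a round is given, the last survey day where none is. This gives six windows (12 weeks) through month 30 in every arm.

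2. **Reporting to the DSMC.** Show events per resident person-time observed, by arm and by age group (0-12 and older in Niger), with all communities as randomized.

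3. **No selection on rounds given.** In Tanzania and The Gambia, do not restrict the comparison to rounds given in both arms. Communities still treated at rounds two or three are those that failed the stopping rule, so that comparison is no longer randomized.

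4. **Mortality over the whole trial.** Compare each formal yearly census list (Section 6.3) with the next and count all deaths in the interval from any update source, per person-year, in every arm. Do not drop deaths first recorded at treatment visits. Treatment visits also update the census (Sections 8.2 and 10.2.2.1), and the yearly update starts from the latest list (Section 10.2.2.2), so using yearly forms alone would lose more deaths in biannual grappes.

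The cost is one more form at visits already made, its data entry and a tabulation of census deaths. One limit remains: communities are not masked, and residents who have not just been treated may report less readily.

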## **7.5 Follow-Up Visits**

The first mass treatment is carried out immediately after the baseline survey. Subsequent follow-up visits are at 6, 12, 18, 24, 30, and 36 months from the first mass treatment. The census lists are updated formally every year prior to the 12, 24, or 36 month survey. The 6, 18, and 30 month surveys will use the census lists for the previous survey when drawing new random samples of sentinel children. The window for each survey is +/- two months.

The exact same procedures as stated for the baseline examination visit are to be followed for all subsequent examination visits. In all cases, mass treatment according to treatment arm is to follow immediately after the survey, to ensure that children are not treated prior to the survey.

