| Arm D Grappes 37-48               | Months 0-2      | Months 0-2                         | Months 6-8     | Months 6-8                         | Months 12-14    | Months 12-14                       | Months 18-20    | Months 18-20                       | Months 24-26    | Months 24-26                       | Months 30-32     | Months 30-32                       | Months 36-38    |

Note: Arms C and D only treat children ages 0-12. A and B are the annual treatment arms. C and D are the biannual treatment arms.

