### 8.1 Overview: Treatment with Azithromycin

The intervention for this trial is community treatment with azithromycin, a single dose antibiotic highly effective against *Chlamydia trachomatis*. Antibiotic sufficient for this trial has been donated by Pfizer international to the National Trachoma Control programs in the three countries. The dosage is 20mg/kg, up to 1 gm in a single dose of either liquid (for children) or tablets (for children able to swallow tablets and adults). In Tanzania and Niger, pregnant women can be treated with azithromycin, but not in The Gambia. In The Gambia, Tanzania and Niger, children below 6 months are not treated with azithromycin but are given topical tetracycline for trachoma.

Azithromycin has been extensively studied for mass use in trachoma control, and has been found to be very effective and well-tolerated. In the ACT trial, no significant adverse effects in children and adults were noted in Tanzania, Egypt and The Gambia. In the STAR trial, which treated adults, no differences in adverse events were noted between topical tetracycline and oral azithromycin. Initial potential concerns for creating clinically significant resistance in other organisms to azithromycin do not appear to be realized. On the basis of these and other studies, each of the countries in this trial have undertaken mass drug administration for their communities, with education to residents that any GI concerns be directed to local health centers and posts for treatment. We anticipate using the same local network to monitor any self reported adverse events, and this is described further in Chapter 14.

Below, we describe in detail the implementation of the intervention in each country setting.

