## 8.5 Monitoring Mass Treatment Coverage

The census data that are obtained and updated yearly will be the primary tool used for monitoring mass treatment coverage. The programs that are built for data entry of the census data will have a report that will be generated that consists of Mass treatment lists for each community, organized as needed for each country (for example, mtaa in Tanzania, grappe in Niger, and village in The Gambia). These master lists are used to record observed treatment coverage for each resident of the community. The data entry of these lists is essential to monitoring coverage as the treatment is underway.

Features of the program will be tailored to each country needs: for example, in Tanzania, as data are entered on coverage, a report can be generated calculating the coverage of children ages to 9.5 years, and if coverage has not hit target, a further report can be generated listing, in random order, all households with at least one resident who has not been treated, and the residents missing treatment. These lists can be used to further guide mass treatment steps as described above, and the data from these reports entered to update coverage. At the end of mass treatment, each community resident should be accounted for as having been treated or not treated and the reason why.

After each community has completed its mass treatment, the full data set on treatment is sent to the principal investigator for each country within a week in order to monitor the success of the treatment team in reaching coverage targets. S/he will review the percent coverage of the community, and if it is over or under target, the reasons why in the file. This will be done within three weeks of mass treatment ending so that if necessary, the treatment team can be re-deployed to the community to improve coverage. If all residents are accounted for, and the resident did not meet treatment coverage targets, the principal investigator will discuss with the treatment team supervisor ways to improve coverage for the second or third rounds (perhaps different timing or working with other community health team members, for example).

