### 8.5.1 Mass Treatment Verification Procedure

Treatment verification is critical to ensuring that coverage levels have been achieved and that reported data is accurate. Treatment verification occurs after each community has completed mass treatment and is conducted by the Community Drug Distributors (CDDs) who initially treated the villages. Post-mass treatment, a CDD pair, consisting of a man and a woman for each sub-village, returns to the village to randomly select a sample of no less than five houses for interview. During the interview, the CDD pair records the number of people residing in the house and how many of

those people received treatment on a treatment spot-check form. After the sample of houses is interviewed, the CDD pair compares the information recorded on the spot-check form to the data in the census treatment books as well as the information gathered from the household's respondent during team members initial visits to the home prior to mass treatment.

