### 12.2.4 Preparation of Data for Transfer to UCSF

#### 12.2.4.1 DATA MANAGEMENT

All treatment and collection data will be entered within four working weeks of collection. Data will be entered and inconsistencies will be resolved by the respective study coordinator or, if necessary, by consultation with the appropriate data collector. Access to any patient information will be protected by a password, or locked in a secure storage room. All data will be backed up upon entry, and forms will be kept until the conclusion of the study.

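### Chapter 14 makes the next six-month survey the first required study review of deaths and hospitalisations after mass treatment, nominally 4.5 to 6 months after the event

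*Protocol*

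**What the plan says.** Chapter 14 counts as serious, within two weeks of a round, gastrointestinal symptoms lasting more than two days, any hospitalisation, and a death in the family. The village health worker writes these on a copy of the census list that the treatment team leaves behind. On what happens next it says: "These events will be reviewed at the next six month survey, and entered into the adverse event data base". The database serves reporting to the DSMC. A resident who needs care is referred to the nearest health centre.

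Section 8.1 says "We anticipate using the same local network to monitor any self reported adverse events" and leaves the detail to Chapter 14.

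Three places set the timing:
- Section 7.5: "In all cases, mass treatment according to treatment arm is to follow immediately after the survey", and "The window for each survey is +/- two months".
- Section 7.6, note to Table 3: "C and D are the biannual treatment arms". In these arms children are dosed at every one of six rounds.
- Section 8.6: every community is treated once more after the three-year survey.

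**The concern.** The protocol attaches definite triggers to other problems. Coverage is reviewed at about three weeks (8.5), a kappa below 0.6 changes a grader's certification (11.1, 17.5.2), and air-swab contamination above 1% requires action (13.8). A death or hospitalisation shortly after a dose has no comparable trigger, so prompt notice to the study depends on someone choosing to raise it.

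Chapter 14 itself allows that serious reports may be rare partly because surveillance has been minimal. It also says that, where use was carefully monitored, gastrointestinal effects were fewer than with topical tetracycline. What is at stake is a definite route for rare serious events, not a known safety signal.

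**Working it through.** **1. Is there an earlier required report?** The sections that could supply one are:
- 8.5: the country principal investigator reviews treatment data after each round ("This will be done within three weeks of mass treatment ending"), but for coverage.
- 8.5.1: "Treatment verification occurs after each community has completed mass treatment and is conducted by the Community Drug Distributors". The household interview counts residents and how many were treated. It does not ask about events, and the visit has no date.
- 13.1 and 13.5: staff can raise problems at bi-weekly meetings. No event obliges them to.
- 13.1: the Executive Committee reviews safety reports every six months. Events enter the database only once the survey review is made, so this does not bring them forward.
- 18.2: the DSMC reviews adverse events at each meeting, at least yearly. An interim call needs a request from a member or the study team.

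None requires a report before the survey.

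**2. Nominal delay.** Events fall on days 0 to 14, that is 0 to 0.5 month after dosing.
- Usual schedule: survey 6 months after dosing, so 6 − 0.5 = 5.5 to 6 months.
- Table 2 (Tanzania), communities dosed the month after their survey: 8 (dose month 2, survey month 7), 16 (3, 8), 23 and 24 (4, 9), 31 and 32 (5, 10). The gap is 5 months, so the lower end is 5 − 0.5 = 4.5 months.
- Overall: about 4.5 to 6 months.

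**3. Effect of the window.** After round 1 the survey is timed from that treatment, so the limits are (6 − 2) − 0.5 = 3.5 and 6 + 2 = 8 months. For later rounds the arithmetic extremes are (18 − 2) − (12 + 2) − 0.5 = 1.5 and (18 + 2) − (12 − 2) = 10 months. These need consecutive surveys at opposite window edges, so they are bounds and not expected values.

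**4. Position relative to the next dose.**
- Communities: 48 + 32 + 48 = 128. Biannual Niger grappes: 12 + 12 = 24, and 24/128 = 18.75%.
- There the next dose follows the review survey at once, for rounds 2 to 6: up to 24 × 5 = 120 community-rounds.
- In the other 128 − 24 = 104 communities the next dose is nominally about six months after that survey.

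**5. The last round.** Surveys end at 36 months (7.5). Treatment given after that survey (8.6) has no scheduled survey behind it, so the Chapter 14 review has no date for that round.

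**6. Screening load of faster reporting.** Residents, from the average sizes in Chapter 3 and section 4.3 (700 for The Gambia): 48 × 375 + 32 × 1,200 + 48 × 700 = 18,000 + 38,400 + 33,600 = 90,000. The protocol gives no death rate. If the crude rate is 8 to 16 per 1,000 per year (an assumption), background deaths in one two-week window are 90,000 × 0.008 × 14/365 = 27.6 to 90,000 × 0.016 × 14/365 = 55.2, or about 28 to 55 per full round. Hospitalisations come on top and cannot be estimated from the protocol.

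**The case against.** The strongest reply is that expedited reporting rules often sit in forms, consent documents or national and IRB requirements. Appendices 1 to 3 and those rules are not shown, and Chapter 14 places dosing under national programmes. This stands as a limit: a faster duty may exist elsewhere. It does not change the operating instruction that field staff read in Chapter 14, which sets the survey as the review point and points to nothing earlier.

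A second reply is that the practical consequence is slight. The survey precedes the next dose, community health workers take part in distribution, care is immediate, and the drug is well tolerated. That is largely right and keeps the point small. In the biannual grappes local review can come before the dose, and early grappes can inform later ones. What is missing there is any set interval for pooling events across grappes or for a central decision.

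Three stronger readings are tempting and should be resisted:
- That the trial has no other safety review. The Executive Committee and DSMC reviews are required too; they come at or after the survey review.
- That children are re-dosed before anyone looks. Section 7.5 puts the survey first.
- That delays of up to ten months are to be expected. Section 7.4 expects non-weather disruptions to last about a week and rescheduling to take up to three weeks.

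**Conclusion.** The point holds as a low-cost safety improvement. Chapter 14 sets the first required study review of post-treatment deaths and hospitalisations at a nominal 4.5 to 6 months after the event. In 24 of 128 communities that review sits directly before the next child dose, and for the treatment after the 36-month survey no scheduled review follows.

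The conclusion rests on the protocol text shown and on the nominal schedule. The expected yield is small. With no untreated arm, sorting related from background events will rest on clinical judgement and on clusters. Nothing here touches randomisation or the outcome analysis.

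**What to change.** Amend the Chapter 14 sentence so that:
1. the village health worker promptly tells the treatment supervisor of any death or hospitalisation within two weeks of treatment;
2. the supervisor passes it to the country principal investigator directly, without waiting for treatment data entry (12.2.4.1 for Niger: "All treatment and collection data will be entered within four working weeks of collection"; 12.4.4.1 says the same for The Gambia);
3. the principal investigator forwards events judged possibly related, or an unusual cluster, to the DSMC chair, and to IRBs under their own rules;
4. the treatment team checks the village list before the next round;
5. for the treatment after the 36-month survey, the supervisor collects the list by contact once the two-week window has closed.

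The six-month review stays as the completeness check for all other events, and care stays under country policy.

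The cost falls on existing staff. Steps 1 to 3 arise only when an event occurs, but most will be background: the principal investigators together would screen about 28 to 55 deaths per full round under the assumed rate, plus hospitalisations. Step 5 needs one contact per community: 32 + 48 = 80 if the section 8.6 statement applies only to Tanzania and The Gambia, 128 if it also covers Niger, and eight more if the PRET Ziada villages are included.
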